**D. Research Design and Methods**

**Clinical trial design:** We will test the primary hypothesis that TRE improves NVC responses and endothelial function in older adults. This hypothesis will be tested by assessing the effects of TRE (10 hours eating window) in community dwelling older adults (55-80 years of age) in a 6-month study. At screening (Visit 0), participants will be evaluated for eligibility criteria, after obtaining informed consent. Individuals

will be asked report medications or supplements intake. Screening assessments and baseline physiological assessments may be conducted at that same visit (baseline, Visit 1) if all eligibility criteria are met, or within 4 weeks of Visit 0 (screening window) at the discretion of the investigator, when eligibility will be again confirmed. After baseline, the first fMRI and dual X-ray absorptiometry (DXA) scan visits will be performed, if the participant opts in to these measurements.

Upon completion of baseline physiologic measurements, all participants will be instructed to maintain TRE for the ensuing 6 months. Participants will be instructed on how to adhere to the TRE protocol. Participants will be evaluated at the Translational Geroscience Laboratory at the end of the protocol, at month 6 (-14/+14 days), when all physiologic assessment will be repeated (Visit 2). If participants terminate the protocol early for any reason, they will be invited to an early termination visit (ETV), which will include repeat physiologic and other evaluations same as in Visit 2. After visit 2, the second fMRI and DXA scan visits will be performed. As stated in the protocol and consent form, MRI and DXA scan visits are optional.

**Power analysis:** Based on our preliminary data analysis, a total of 27 eligible participants will provide 80% power for detecting a decrease of 7.4 in fNIRS against the null hypothesis of no change. A standard deviation of 13.1 was used in the calculation. After adjusting for a 20% dropout, the total of 32 participants will be enrolled. We will use intent-to-treat approach, wherein every participant will be included in the analysis regardless of whether participant is on or off the TRE for the final visit. To control for potential confounding, we will account for BMI, depression, the use of opiates, and other non-exclusive chronic conditions.

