**Body composition and physical exam:** Weight and body composition will be acquired using a bioimpedance scale (Tanita Body Composition Analyzer BC-418) at each study visit. Total daily energy expenditure (TDEE) will be estimated using the Mifflin-St. Jeor equation [22-24] multiplied by the appropriate factor according to PAL. Estimated dietary intakes and TDEE will be used to determine whether a participant was in a hypocaloric, eucaloric, or hypercaloric state during the intervention. Moreover, we will collect data on blood pressure and heart rate. Blood glucose and cholesterol will be determined using the Lipid Panel Plus panel from Piccolo Xpress. Optionally, participants may choose to undergo a DXA scan to obtain body composition (% fat mass and % lean mass) and bone density estimates. This medical imaging technique uses low levels of X-rays to measure bone density and body composition. DXA scans will take place at the Oklahoma Shared Clinical and Translational Resources (OKC, OK).

**Study 1: Determine NVC responses using functional near-infrared spectroscopy (fNIRS), electroencephalography (EEG), and dynamic retinal vessel analysis (DVA):**

We will use **fNIRS** recordings to assess NVC responses elicited during the performance of a standardized cognitive n-back test [25]. For the *n-back* task, the participant is required to monitor a series of letters (or numbers) on the computer screen and to respond by clicking the computer mouse right button when the presented letter matches the letter *n*-steps back. We will also record the NVC responses using the fNIRS during standardized motor task, or other standardized stimulation paradigm. We will assess neuronal activity during a similar n-back paradigm (series of numbers) to evaluate the neuronal component of the NVC using the **EEG**.

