**Cognitive performance:** For cognitive assessment, all NIH Toolbox tests will be organized into two groups of fluid abilities (i.e., working memory, processing speed, episodic memory, and two aspects of executive functioning) and crystallized abilities (i.e., dependent upon past learning and experience), resulting in Standard Scores for these superordinate categories, as well as a total Composite score of all tests. We will use Standard Scores and Composite scores for analysis. These norms were previously reported to align with the age-corrected normative data for the traditional neuropsychological measures, and also because the time interval between baseline Visit 1 and final Visit 2 would not be affected by the participant's race/ethnicity or educational level. We will use GLM for between-group factor and repeated measures (within group) factor. For post-hoc analysis, we will perform the Bonferroni test. The level of significance will be regarded as  $p < 0.05$ .

**Functional magnetic resonance imaging (fMRI)** will be used to quantify patterns of activation associated with brain networks reorganization before and after treatment on each participant. Structural and functional imaging data will be acquired. Structural T1-weighted scans, T2 scans, and scans assessing tissue characterization will be acquired. Functional scans will be acquired with a single-shot EPI sequence. Functional runs will be collected using a cognitive performance task such as the N-back task, and will have a duration of 21 minutes or less. Each MRI session will be less than 2 hours within the magnet. A repeated measures design (baseline and post-TRE) will be conducted for each participant. Additional baseline data will be obtained for secondary correlations. Besides that, a sensitivity analysis testing the comparison of post-TRE only will be additionally conducted.

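### The design puts every participant on TRE and provides no control group, so Visit 1 to Visit 2 changes in NIH Toolbox scores and n-back-driven measures mix any TRE effect with retest learning

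*Protocol*

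**What the plan says.** Section D (Clinical trial design) states: "Upon completion of baseline physiologic measurements, all participants will be instructed to maintain TRE for the ensuing 6 months". The baseline assessments are repeated at Visit 2, at month 6. No allocation or comparison group is described. The power analysis in the same section is framed "against the null hypothesis of no change", with 27 evaluable and 32 enrolled participants in total.

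Several measures depend on tasks that can be learned. Study 1 uses fNIRS "to assess NVC responses elicited during the performance of a standardized cognitive n-back test", and for EEG it says "We will assess neuronal activity during a similar n-back paradigm". The optional fMRI may also use the n-back (Section M). Study 3 uses NIH Toolbox tests. For these, Section M says "We will use Standard Scores and Composite scores for analysis" and justifies the choice by age-corrected norms and by reference to race/ethnicity and education. The protocol mentions no practice run, alternate form, second baseline or retest-corrected score.

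Section M also specifies a TRE-versus-control group effect for fNIRS, two-sample tests for EEG, and a between-group factor with repeated visits for DVA, endothelial function and cognition. Only its fMRI paragraph describes a purely within-participant comparison before and after TRE.

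**The concern.** In a single-group before-after comparison, whatever else changes between the visits is added to the treatment effect. For tasks that people improve at by repetition, one such change is predictable: at Visit 2 every participant has already done the task at Visit 1. A Toolbox gain could then be read as a cognitive benefit of TRE when part or all of it is familiarity.

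The same holds for a haemodynamic or EEG signal evoked by the n-back, because a better-practised task may evoke a different response. fNIRS is the measure on which the trial is powered, and Section M says the data will support a grant application. The interpretation therefore matters even in a small study.

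**Working it through.** **Step 1: which contrast was the trial sized for?** Inputs from Section D (Power analysis): change 7.4, SD 13.1, 80% power, 27 evaluable. The power paragraph states no alpha, so two-sided 0.05 is assumed.

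- Standardised change: 7.4 / 13.1 = 0.565.
- Paired (one-sample) t-test: noncentrality = 0.565 × √27 = 2.94 on 26 degrees of freedom. Power is 80.7%, and 27 is the smallest n that reaches 80%. The stated figure is reproduced.
- Two-arm comparison with 13.1 as the SD in each arm: the normal approximation gives 2 × 24.6 = 49.2, so 50 per arm. The t-test gives 51 per arm, or 102 evaluable.
- Enrolment: 27 × 1.2 = 32.4, which matches the stated total of 32.

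So 27 fits a single-group change from baseline and does not fit a TRE-versus-control comparison.

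**Step 2: what does that contrast estimate?** Mean (Visit 2 − Visit 1) = TRE effect + retest effect + any other time effect. With everyone treated, the first two terms cannot be separated. A control group tested at both visits would cancel the retest effect common to both groups, but Section D provides none.

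**Step 3: how much could it matter?** The protocol gives no retest gain, so the drift r (in SDs of the change) is an assumption. With no TRE effect, n = 27 and a two-sided paired t-test at 0.05, the noncentrality is r × √27:

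| Assumed drift r | Noncentrality | Probability of p < 0.05 |
|---|---|---|
| 0 | 0 | 5.0% |
| 0.1 | 0.52 | 7.9% |
| 0.2 | 1.04 | 17.0% |
| 0.3 | 1.56 | 32.4% |
| 0.4 | 2.08 | 51.7% |
| 0.5 | 2.60 | 70.6% |

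**Step 4: direction.** For Toolbox scores, learning raises the score, which is the direction read as benefit. For n-back fNIRS the protocol does not fix a direction: the power analysis speaks of "detecting a decrease of 7.4 in fNIRS", while Section M looks for increased activation. No beneficial direction is defined for EEG. Learning could therefore also hide an effect. If a true change of 0.565 SD is opposed by a drift of 0.1, 0.2 or 0.3 SD, power at n = 27 falls from 80.7% to 64.3%, 44.7% or 26.3%.

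**Step 5: which endpoints are exposed?** Exposed: Toolbox scores, n-back fNIRS, n-back EEG, and fMRI if it uses the n-back. Not dependent on these tasks: flicker-light DVA, FMD, laser speckle, and fNIRS during the motor task.

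**The case against.** The strongest reply is that Section M already compares TRE with control, and a control group tested at both visits would remove common learning. A reader might infer that Section M credits the visit-to-visit gain to TRE. For cognition, fNIRS and EEG it does not, because it names group comparisons. Sections I and O also speak of groups, and the Specific Aims mention age-matched controls for the serum experiment. What does not stand is the protection itself: Section D has everyone on TRE, and the sample size fits one group.

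Four other limits are fair.

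- A reader might infer that learning produces false benefit in fNIRS and EEG. The documents do not fix the direction, so only confounding can be claimed.
- It is not stated that Visit 1 is a participant's first exposure, and recruitment draws partly on an ongoing ageing study. Nor is it stated that n-back accuracy or reaction time is stored; participants respond by mouse click, and no more is said.
- The percentages rest on assumed drifts, a paired test and an n chosen for fNIRS. The planned analyses use FDR correction for fNIRS and EEG, and a GLM with Bonferroni post-hoc tests for cognition.
- The primary hypothesis in Section D concerns neurovascular coupling and endothelial function, not cognition.

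It may also be said that practice runs belong in an operating procedure. But the protocol gives its own rationale for the Toolbox scores, and that rationale does not address prior exposure. Practice must also precede the first recording, so a later analysis plan cannot supply it.

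**Conclusion.** The point holds on a single-arm reading, which Section D and the reproduced sample size support. It is firmest for the Toolbox scores, where the bias runs towards apparent benefit. For n-back fNIRS and EEG, and fMRI if it uses the n-back, the change is confounded in an unknown direction. The size is not known from the document: 17% to 32% false-positive results is an illustration at assumed drifts of 0.2 to 0.3 SD of the change, not an estimate for this trial. If controls tested on the same schedule are in fact intended, common learning largely cancels. Section D and its sample size would then be what needs correcting. Either way, Sections D and M cannot both stand as written.

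**What to change.** First, reconcile Section D with Section M: state whether a control group tested at both visits exists, and align the models and sample size with the answer. If the trial is single-arm:

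1. Give a short unrecorded n-back practice block at Visit 0, or before the first recording at Visit 1 where the two visits coincide. Add practice on the Toolbox tasks where feasible. This reduces learning but does not remove it.
2. Store and report n-back accuracy and reaction time at both visits. Label any fNIRS model adjusted for change in n-back performance as exploratory: performance is measured after treatment, and the central hypothesis expects TRE to improve cognition, so the adjustment could remove part of a real effect.
3. State that, without a concurrent control, changes in cognition and n-back-driven measures will be reported as uncontrolled change from baseline and not as a TRE effect. Read them beside DVA, FMD and laser speckle, which do not depend on task learning.

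The cost is a few minutes of visit time for the n-back block, one exploratory model and a more modest cognitive claim. The time needed for Toolbox practice is not known from the protocol, hence the qualification in item 1.

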**N. Data and Safety Monitoring Plan**

The PI team will provide direct oversight to ensure that this low-risk trial is conducted according to the protocol.

**Clinicaltrials.gov**

This study is registered on clinicaltrials.gov under identifier NCT06019195.

**O. Data Sharing**

The primary objective is to publish any significant research results that will be generated during this project in a peer-reviewed journals. The results of this project will be submitted to local, national, and international scientific conferences and meetings and accepted abstracts will be presented either orally or by poster at these meetings. The results will also be disseminated by presentation at seminars organized by the Oklahoma Clinical and Translational Sciences Institute.

The results may also be uploaded to scientific online repositories such as PhysioNet as requested by the journal. In that case, all data will be de-identified and labeled by group+number (for example Control1, Control2, TRE1, TRE2, these IDs will be different from study IDs stored on the servers at the OUHSC) and supported by subjects' age and sex, treatments/comorbidities.

**P. Confidentiality**

All clinical and digital data obtained during the study will be stored electronically in a HIPAA compliant storage facility including OUHSC shared drive, encrypted external hard drives, password-protected OUHSC REDCap database. Access to PHI data will be limited to study staff only.

